### Randomisation and allocation concealment

Randomisation will be performed using a computer-generated sequence with a 1:1 allocation ratio, employing permuted blocks of variable size (4–8 participants) to reduce allocation predictability. To minimise selection bias, randomisation will be stratified by age (<50 vs ≥ 50 years), given the established influence of age on FM outcomes.

Allocation concealment will be maintained through a centralised, web-based system (REDCap, Vanderbilt University), operated by an independent researcher not involved in intervention delivery or outcome assessment. This system provides automatic participant assignment with timestamped allocation records, ensuring transparency and traceability.

If web-based randomisation is unavailable, a validated contingency procedure will be implemented using sequentially numbered, opaque, sealed envelopes (SNOSE) prepared off-site by an independent statistician. Envelopes will be tamper-proof, opaque, and opened sequentially only after participant enrolment and baseline assessment.

### Blinding

Outcome assessors, the principal investigator, and the study statistician will remain blinded to group allocation until database lock. Randomisation will be executed centrally through the secure REDCap system. Group-specific content within the digital platforms will be activated and managed by an unblinded administrator who has no role in outcome assessment, intervention supervision, data cleaning, or statistical analysis.

Because of the nature of non-pharmacological digital exercise interventions, complete blinding of participants and treating physiotherapists is not feasible. To minimise performance bias and expectancy effects, the study employs an active comparator (sham digital experience). Participants in the control arm will access a visually identical platform interface that provides general fibromyalgia self-management education and non-specific physical activity guidance, but without the active components (AI-driven real-time biomechanical feedback and structured PNE modules).

Participants will be informed that the trial compares two digital health management approaches, without disclosing any superiority hypothesis related to the AI/PNE intervention. They will be instructed not to reveal their perceived group allocation during outcome assessments. Technical support staff and adherence monitors will not be involved in outcome data collection.

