### Pain neuroscience education (PNE)

In parallel, Concurrently, participants will complete one asynchronous online module per week (https://proyectofibrobrain.org). The 12 sequential modules, adapted from validated frameworks [13,14,24], address topics such as nociplastic pain, central sensitisation, neuroplasticity, and psychosocial modulators [15,24,25]. Content incorporates multimedia resources, clinical metaphors (e.g., the “alarm system”), and guided reflection activities. Each module concludes with comprehension questions and self-assessment exercises to reinforce learning [26,27]. The modules were co-designed with patients with FM to ensure linguistic, cultural, and contextual relevance [13].

**Control group**Control participants will receive enhanced usual care according to clinical guidelines [3,8,9], typically including analgesics (paracetamol, tramadol), antidepressants (amitriptyline, duloxetine), anticonvulsants (pregabalin, gabapentin), and general lifestyle advice. In addition, they will use the same digital platforms with a visually identical interface and will receive standard, non-specific educational materials on fibromyalgia self-management and general physical activity guidance (without AI-guided exercise feedback or pain neuroscience education modules). Concomitant care will be documented systematically.

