### Intervention fidelity and adherence monitoring

All physiotherapists will complete a standardized training program and adhere to a detailed intervention manual specifying session structure, therapeutic content, and delivery protocols. Intervention fidelity will be evaluated monthly by an independent investigator uninvolved in intervention delivery. Audits will include digital log reviews (frequency, duration, accuracy), random checks of therapist documentation, and verification of protocol compliance.

Protocol adherence will be deemed satisfactory when ≥90% of planned components are delivered as outlined in the manual. Identified deviations will trigger corrective actions such as targeted feedback, refresher training, and additional supervision until compliance is restored. Fidelity indicators—including adherence rates, frequency of deviations, and corrective measures—will be summarised descriptively and reported in the Results section to document intervention integrity [38].

Participant adherence will be monitored automatically through the digital platforms. Participants will be considered adherent if they complete ≥80% of prescribed sessions (≥29/36 exercise sessions and ≥10/12 PNE modules). Automated SMS or email reminders will be issued for missed sessions, and non-adherent participants will receive motivational follow-up from the research team to address barriers.

Control group participants’ engagement (login frequency, material access, and time spent on the platform) will be monitored equivalently to ensure comparable exposure time. Study staff will conduct monthly check-ins to verify participation and reduce attrition bias across groups.

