### Outcomes

Outcome selection followed the IMMPACT recommendations for chronic pain clinical trials [28] and was tailored to the characteristics of FM and the digital delivery format (Table 1).

**Table 1 pone.0349017.t001:** Description of the measurements.

Variable Category	Variable	Dimension	Indicator	Value
**Sociodemographic Data**	Age	Chronological age	Number of complete years	18 to 65 years
	Gender	Gender identification	Participant-reported gender	Male / Female
	Educational level	Formal schooling level	Highest level completed	Primary / Secondary / Technical / University / Postgraduate
	Residence location	Geographical context	Living area	Urban / Rural
	Access to technology	Digital inclusion	Availability of internet-connected devices	Yes / No
	Employment status	Work situation	Current working status	Employed / Unemployed / Informal / Retired
**Clinical Data**	Diagnosis duration	Time since FM diagnosis	Time elapsed since official diagnosis	Numerical (months)
	Pharmacological treatment	Medication type and dose	Use of prescribed drugs	Analgesics, antidepressants, anticonvulsants (type, dose, frequency)
	Comorbidities	Associated diseases	Presence of additional chronic conditions	Yes / No (specify if relevant)
**Primary Outcomes**	Pain intensity	Subjective pain perception	Visual Analogue Scale (VAS)	0 (no pain) to 10 (worst imaginable pain)
**Secondary Outcomes**	Impact of FM	Functional limitation and symptom severity	Total score of the FIQ-R	0 to 100 (higher scores indicate worse impact)
	Lower limb function	Strength and endurance	30-Second Sit-to-Stand Test	Number of repetitions in 30 seconds
	Quality of life	Health-related QoL	EQ-5D index	−0.59 to 1.0 (higher = better QoL)
	Anxiety	Psychological distress	Numeric Rating Scale for Anxiety (NRS-A)	0 (no anxiety) to 10 (worst possible anxiety)
	Adherence barriers	Perceived obstacles to treatment	Treatment Adherence Barriers Questionnaire	Categorized: logistical, motivational, contextual, etc.

Table note: Abbreviations: FM = Fibromyalgia; VAS = Visual Analogue Scale; FIQ-R = Revised Fibromyalgia Impact Questionnaire; EQ-5D = EuroQol-5 Dimensions; NRS-A = Numeric Rating Scale for Anxiety.

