### Data monitoring and auditing

Given he minimal-risk nature of the intervention (exercise and education), a full independent Data Monitoring Committee (DMC) will not be convened. Instead, an independent safety monitor external to the study team and with expertise in rehabilitation and clinical research will periodically review safety data, including adverse events and protocol deviations, to ensure participant protection.

Safety and adherence data will also be reviewed monthly by the supervising physiotherapists and the principal investigator. Serious adverse events will be reported immediately to the ethics committee and documented according to institutional and regulatory requirements.

Although external audits are not planned, the study may be subject to internal audits by the sponsoring institution, Universidad Santiago de Cali, or by the ethics committee if required. All monitoring and audit reports will be archived and made available upon request.

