### Strengths and limitations of this study

This study presents an innovative tele-rehabilitation program that integrates artificial intelligence guided exercise and Pain Neuroscience Education (PNE), providing a novel, patient-centered approach to fibromyalgia (FM) management.The fully remote design enhances accessibility and scalability, particularly benefiting underserved and rural populations.The use of validated and widely recognized outcome measures ensures methodological rigor and facilitates comparison with existing research.The relatively small sample size may limit the generalizability of the findings.Blinding of participants, outcome assessors, and statistical analysis strengthens internal validity; however, potential variability in adherence to digital interventions may introduce bias.

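### The principal investigator is listed as blinded but reviews monthly safety and adherence data that, at participant level, would show the arm; participants are credited as blinded although the Blinding section says full blinding is not feasible

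*Protocol article*

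**What the plan says.** **Principal investigator.** The Blinding section lists three blinded roles: "Outcome assessors, the principal investigator, and the study statistician will remain blinded to group allocation until database lock". The Data monitoring and auditing section then states: "Safety and adherence data will also be reviewed monthly by the supervising physiotherapists and the principal investigator".

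**What adherence data consist of.** Intervention fidelity and adherence monitoring defines adherence by session and module counts: "Participants will be considered adherent if they complete ≥80% of prescribed sessions (≥29/36 exercise sessions and ≥10/12 PNE modules"). For controls, the same section says that "engagement (login frequency, material access, and time spent on the platform) will be monitored equivalently". The control-group paragraph, under Pain neuroscience education (PNE), says that the control platform comes "without AI-guided exercise feedback or pain neuroscience education modules".

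**Participants.** The Blinding section accepts that "complete blinding of participants and treating physiotherapists is not feasible". The abstract and the trial design section describe the trial as assessor-blinded only. The closing section on strengths and limitations says: "Blinding of participants, outcome assessors, and statistical analysis strengthens internal validity". The primary outcome is pain on a 0 to 10 VAS, whose dimension in Table 1 is "Subjective pain perception".

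**The concern.** Two statements about blinding do not fit the rest of the text.

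First, the principal investigator is promised to be blind until database lock but receives data each month whose form depends on the arm. If those data are at participant level, the promise cannot be kept, and the trial report would claim a blinded role that was not blinded.

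Second, participant blinding is presented as a strength of internal validity. Participants rate the primary outcome themselves, so blinding the assessor and the statistician does not protect that rating from expectancy. A reader who relies on the strengths section would credit the deciding outcome with more protection than the design gives it.

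**Working it through.** No arithmetic applies. The check sets the statements side by side.

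**A. Principal investigator**

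1. Claimed status: blinded to allocation until database lock (Blinding).
2. Access: monthly review of safety and adherence data (Data monitoring and auditing). Nothing there or elsewhere says that the data are pooled across arms or masked for this role.
3. Form of the adherence data by arm (Intervention fidelity and adherence monitoring; control-group paragraph):
   - Intervention: exercise sessions completed out of 36 and PNE modules completed out of 12.
   - Control: login frequency, material access and time on the platform. This arm has no PNE modules and no AI-guided exercise feedback.
4. A participant-level line with session and module counts can therefore only belong to the intervention arm, and a line without them points to control. This is an inference from the content; no section says it outright.
5. Safety data offer a second route. Under Adverse event monitoring and reporting, the platforms raise an alert when a session is left incomplete because of symptoms. Under Discontinuation criteria, exercise intensity may be adjusted or sessions suspended. Prescribed exercise sessions are described only for the intervention arm, so a participant-level record of this kind also points to the arm.
6. Participant codes do not help. A coded record still shows the arm by its content.
7. Result: statements 1 and 2 are compatible only if the monthly review is pooled or masked, and the text does not say that it is.

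**B. Participants**

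1. Blinding section: complete blinding of participants is not feasible.
2. Abstract and trial design: assessor-blinded.
3. Mitigation in the Blinding section: a control platform that looks the same, and no disclosure of the superiority hypothesis. This is partial masking.
4. Assessment of blinding: participants and assessors guess the allocation at week 13, and Bang's index is computed. This measures masking afterwards and does not establish it.
5. Strengths section: participant blinding is claimed without qualification. The limitations named there are sample size and variable adherence. Self-report by participants who are not fully blinded is not among them.
6. Result: statement 5 contradicts statement 1, and the contradiction concerns the people who produce the primary outcome.

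**The case against.** The strongest reply is that the monitoring section does not say what form the monthly data take. An article may leave report formats to a fuller protocol or monitoring plan, and control engagement is said to be monitored equivalently. This stands in part: it is not shown that the principal investigator will be unblinded. What remains is that the article makes a firm promise in one section and describes access that would break it in another, with nothing to reconcile the two.

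A reader might go further in four ways that the document does not support:

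- **That all 50 allocations would be known at the first monthly review.** This would need full enrolment and platform activity by then, and no section says so.
- **That an unblinded principal investigator would decide protocol deviations or exclusions.** No section gives that role such decisions. An independent investigator audits fidelity, the independent safety monitor reviews deviations, and the ITT population includes everyone randomised.
- **That the principal investigator and the physiotherapists hold a joint review.** Both are named as reviewers, but a shared meeting is not stated.
- **That assessor or statistician blinding is compromised.** Nothing in the text withdraws it, and the principal investigator is not named as an outcome assessor.

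On participants, the reply is that the working sections are candid, that the Blinding section names expectancy effects and acts on them, and that the strengths sentence governs no procedure. All of that is true, and it limits the consequence. It does not make the unqualified claim correct.

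**Conclusion.** The point holds as two inconsistencies in the text.

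The principal investigator's blinding is not secured by the design as written. This rests on one assumption: that the monthly review shows participant-level data without masking. If it is pooled or masked, the inconsistency disappears once the article says so. If not, the review would reveal the arm of each participant reviewed.

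The participant-blinding claim in the strengths section is wrong as worded and needs no assumption. The look-alike platform and undisclosed hypothesis support a claim of partial masking at most.

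The document gives no basis for sizing an expectancy effect on the VAS, so none is offered. The primary analysis, the sample size and the assessor-blinding procedure are unaffected. What is at stake is whether the blinding reported for this trial is the blinding it has.

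**What to change.** 1. **Data monitoring and auditing.** State that the principal investigator receives only arm-pooled or masked summaries, covering both adherence and safety data; masking adherence alone would leave the symptom-alert route open. Leave participant-level review to the physiotherapists, who are already unblinded, and to the independent safety monitor. Log any unblinding of the principal investigator that safety requires.
2. **Alternative.** If the principal investigator must see participant-level data, remove that role from the blinded list in the Blinding section.
3. **Strengths and limitations.** Delete participants from the blinding claim. Add as a limitation that the primary outcome is self-reported by participants who are not fully blinded.

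**Cost.** The monthly report changes recipients or format, and the blinding statement becomes slightly less favourable. The safety monitor is described as reviewing safety data periodically, including adverse events and deviations, so any monthly adherence review by that monitor would have to be added to the remit. The article states that nobody had been recruited at submission; if that is still so, the change can precede the data.

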### Assessment of blinding

At the post-intervention assessment (Week 13 ± 7 days), both participants and outcome assessors will be asked to guess group allocation and to rate their confidence in that guess. Bang’s Blinding Index will be calculated to quantify the success of blinding

### Interventions

Participants allocated to the intervention arm will undertake a 12-week tele-rehabilitation program combining AI-guided exercise and Pain Neuroscience Education (PNE). This multimodal approach targets both physical and cognitive emotional dimensions of FM, aiming to promote physical activation, pain reconceptualisation, and self-efficacy [6,7,13].

### AI-guided exercise with computer vision

Participants will complete three home-based sessions per week (30–40 minutes each) via a digital platform integrating artificial intelligence and computer vision (https://rehbody.net/) Rehbody is a clinically validated telerehabilitation platform that uses the participant’s device camera to capture and analyse movement patterns through AI-driven motion tracking. The system identifies joint angles, range of motion, and posture deviations in real time, providing immediate audiovisual feedback to ensure correct technique and prevent injury. It automatically adjusts exercise difficulty based on individual performance metrics and adherence data. All data are encrypted and stored on secure servers compliant with international data protection standards (GDPR). The program follows four progressive phases: adaptation (weeks 1–3), progression (weeks 4–6), consolidation (weeks 7–9), and maintenance (weeks 10–12) [16,18]. Exercises evolve from sit-to-stand with chair support and unweighted deadlifts to glute bridges, incline push-ups, and loaded Romanian deadlifts (S2 Appendix). All sessions are remotely supervised by a licensed physiotherapist who reviews adherence reports and responds to alerts [18,23].

### Pain neuroscience education (PNE)

In parallel, Concurrently, participants will complete one asynchronous online module per week (https://proyectofibrobrain.org). The 12 sequential modules, adapted from validated frameworks [13,14,24], address topics such as nociplastic pain, central sensitisation, neuroplasticity, and psychosocial modulators [15,24,25]. Content incorporates multimedia resources, clinical metaphors (e.g., the “alarm system”), and guided reflection activities. Each module concludes with comprehension questions and self-assessment exercises to reinforce learning [26,27]. The modules were co-designed with patients with FM to ensure linguistic, cultural, and contextual relevance [13].

**Control group**Control participants will receive enhanced usual care according to clinical guidelines [3,8,9], typically including analgesics (paracetamol, tramadol), antidepressants (amitriptyline, duloxetine), anticonvulsants (pregabalin, gabapentin), and general lifestyle advice. In addition, they will use the same digital platforms with a visually identical interface and will receive standard, non-specific educational materials on fibromyalgia self-management and general physical activity guidance (without AI-guided exercise feedback or pain neuroscience education modules). Concomitant care will be documented systematically.

### Intervention fidelity and adherence monitoring

All physiotherapists will complete a standardized training program and adhere to a detailed intervention manual specifying session structure, therapeutic content, and delivery protocols. Intervention fidelity will be evaluated monthly by an independent investigator uninvolved in intervention delivery. Audits will include digital log reviews (frequency, duration, accuracy), random checks of therapist documentation, and verification of protocol compliance.

Protocol adherence will be deemed satisfactory when ≥90% of planned components are delivered as outlined in the manual. Identified deviations will trigger corrective actions such as targeted feedback, refresher training, and additional supervision until compliance is restored. Fidelity indicators—including adherence rates, frequency of deviations, and corrective measures—will be summarised descriptively and reported in the Results section to document intervention integrity [38].

Participant adherence will be monitored automatically through the digital platforms. Participants will be considered adherent if they complete ≥80% of prescribed sessions (≥29/36 exercise sessions and ≥10/12 PNE modules). Automated SMS or email reminders will be issued for missed sessions, and non-adherent participants will receive motivational follow-up from the research team to address barriers.

Control group participants’ engagement (login frequency, material access, and time spent on the platform) will be monitored equivalently to ensure comparable exposure time. Study staff will conduct monthly check-ins to verify participation and reduce attrition bias across groups.

### Discontinuation criteria

Participants may discontinue the intervention if they experience a serious adverse event (SAE), clinically significant deterioration, voluntary withdrawal, or persistent non-adherence (>30% missed sessions). For moderate adverse symptoms, exercise intensity may be adjusted, or sessions temporarily suspended. All modifications will be recorded. Participants who discontinue the intervention will be encouraged to complete follow-up assessments.

### Adverse event monitoring and reporting

All adverse events (AEs) occurring from enrolment to final assessment will be recorded, regardless of their relationship to the intervention. AEs are defined as any untoward medical occurrence, while SAEs include events resulting in death, life-threatening conditions, hospitalisation, or persistent disability.

Participants will be instructed to report any new symptoms or health changes. The digital platforms (Rehbody.net and ProyectoFibroBrain.org) automatically generate alerts when sessions are incomplete due to reported symptoms, prompting physiotherapist follow-up.

All AEs and SAEs will be documented in case report forms, detailing onset, duration, severity, relatedness, and actions taken. SAEs will be reported to the ethics committee within 24 hours. Safety data will be summarised descriptively by group in the final report, following CONSORT recommendations.

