### Permitted and prohibited co-interventions

Participants in both groups may continue pharmacological treatments prescribed by their primary care providers, including analgesics, antidepressants, or anticonvulsants commonly used in FM management. They will be instructed not to initiate any new structured physical therapy, exercise program, or cognitive behavioural therapy during the trial. Engagement in such interventions outside the study protocol will be considered a protocol deviation.

At each assessment point, participants will report any additional treatments, medications, or health-related changes. These data will be documented and included as potential covariates in subsequent analyses.

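### Adverse-event detection appears more intensive in the intervention arm, so the descriptive by-group safety summary is open to ascertainment bias

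*Protocol article*

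**What the plan says.** The section on adverse event monitoring and reporting commits the trial to recording every adverse event from enrolment to the final assessment. It names two routes.

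- Self-report, with no restriction by arm: "Participants will be instructed to report any new symptoms or health changes".
- Platform alerts: the platforms "automatically generate alerts when sessions are incomplete due to reported symptoms", and each alert leads to follow-up by a physiotherapist.

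The same section then plans the output: "Safety data will be summarised descriptively by group in the final report".

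Two further contacts are described elsewhere.

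- The section on permitted and prohibited co-interventions states: "At each assessment point, participants will report any additional treatments, medications, or health-related changes". The assessment points are weeks 0 and 13, and the stated use of these data is as possible covariates.
- The section on intervention fidelity and adherence monitoring states: "Study staff will conduct monthly check-ins to verify participation and reduce attrition bias across groups".

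The exercise schedule is given for the intervention: "Participants will complete three home-based sessions per week (30–40 minutes each" is the start of the sentence. That section also gives the supervising physiotherapist the task of responding to alerts. Controls use the same platforms but receive general material "without AI-guided exercise feedback or pain neuroscience education modules". Their use is tracked by logins, material accessed and time spent.

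**The concern.** A comparison of adverse-event counts between arms is interpretable only if events are looked for equally hard in both. Here the one symptom-triggered route that operates during the 12 weeks and brings in a clinician depends on a session being interrupted. The article prescribes sessions to one arm only. A symptom that stops an intervention participant's exercise leads to a physiotherapist contact and probably an entry on the case report form. The same symptom in a control, on a day with nothing scheduled, is recorded only if the participant volunteers it or recalls it at week 13.

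The table could then show more harm under the intervention when the true risks are equal. It could also leave a real excess indistinguishable from closer observation. This matters because safety is among the benefits that the abstract and the discussion claim for the AI-guided approach. Events that were never asked about cannot be recovered after the trial.

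**Working it through.** The article states no adverse-event rate or detection rate, so there is no figure to reproduce. The check is which routes exist in which arm, followed by an illustration of size.

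**1. Routes by arm, as described**

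| Route | Intervention | Control | Limits |
|---|---|---|---|
| Self-report of new symptoms | yes | yes | passive instruction |
| Health changes at assessments | yes | yes | weeks 0 and 13 only; kept as covariates |
| Monthly check-ins | yes | yes, on the natural reading | purpose is participation and attrition |
| Alert on a symptom-interrupted session, with physiotherapist follow-up | yes | no prescribed session described that could trigger it | one arm, by inference |

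**2. Scheduled occasions on which an alert could arise**

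Exercise: 3 per week × 12 weeks = 36. PNE: 12 modules. The article's adherence thresholds agree with these totals: 0.8 × 36 = 28.8, rounded up to 29, and 0.8 × 12 = 9.6, rounded up to 10. An intervention participant therefore has 36 occasions, or 36 + 12 = 48 if an unfinished module counts as a session. None is prescribed for a control. These are opportunities, not expected alerts.

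**3. Illustration of size (all rates assumed)**

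Take the same true risk *p* in both arms. Let *s* be the probability that the shared routes record an event, and *a* the probability that the alert records one that the shared routes miss.

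- Recorded share, control: *s*
- Recorded share, intervention: 1 − (1 − *s*)(1 − *a*)
- Spurious ratio: [1 − (1 − *s*)(1 − *a*)] / *s*

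With 25 per arm (from the sample size section) and an assumed *p* = 0.40, 10 participants per arm truly have an event.

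| *s* | *a* | Intervention recorded | Control recorded | Ratio |
|---|---|---|---|---|
| 0.5 | 0.3 | 6.5 | 5.0 | 1.30 |
| 0.5 | 0.6 | 8.0 | 5.0 | 1.60 |
| 0.7 | 0.3 | 7.9 | 7.0 | 1.13 |
| 0.7 | 0.6 | 8.8 | 7.0 | 1.26 |
| 0.9 | 0.3 | 9.3 | 9.0 | 1.03 |
| 0.9 | 0.6 | 9.6 | 9.0 | 1.07 |
| 1.0 | any | 10.0 | 10.0 | 1.00 |

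One row worked: *s* = 0.7, *a* = 0.6 gives 1 − 0.3 × 0.4 = 0.88, and 0.88 / 0.7 = 1.26.

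The ratio does not depend on *p*. A more unfavourable assumption, 50% detection in controls against 90% in the intervention arm (*s* = 0.5, *a* = 0.8), gives 0.9 / 0.5 = 1.8. The ratio returns to 1.00 only if the shared routes catch everything or the alert adds nothing. It never falls below 1.

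**4. After the change**

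If the comparison uses only events solicited by the same question on the same schedule, *a* drops out. The expected ratio under equal risk is then 1.00, for example 7.0 against 7.0 at *s* = 0.7.

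**The case against.** A reader might go further and infer that adverse events are found through alerts that only the intervention arm has, that no physiotherapist ever looks at controls, and that the safety table is therefore biased. The documents do not support that.

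- The alert is an added route. Self-report, the assessments and the check-ins are not restricted by arm.
- No sentence confines the alert to one arm. The trial design section puts all participants on the same platforms with the same data capture. The confinement is a strong inference from where sessions and alert response are described.
- The data monitoring section has the supervising physiotherapists and the principal investigator review safety and adherence data monthly, and an independent safety monitor review them periodically. Neither review is limited to one arm. Such review examines events already recorded, however, and does not find those that were never reported.
- The exercise is remotely supervised, so the trial makes no claim about unsupervised exercise.

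Three further points deserve weight. The alert depends on a reported symptom, so it partly duplicates self-report and may add little. Symptoms caused by exercising are real harms of the intervention, not artefacts. The summary is descriptive, with no test.

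These points limit the size and the certainty, but the asymmetry remains. A by-group table is read as a comparison even without a test. It cannot separate exercise-related harm from closer observation unless the detection source is recorded.

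It can also be said that a full protocol or operations manual may hold a common adverse-event script. That is possible, and missing detail alone would not be a finding. The point rests on what the article does state: an extra detection route tied to sessions, feeding a between-group summary.

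**Conclusion.** The concern holds in a limited form. Adverse-event detection appears more intensive in the intervention arm, and the descriptive by-group summary is open to ascertainment bias, most likely towards more recorded events under the intervention. This rests on two readings: that controls have no prescribed session that could trigger an alert, and that the check-ins do not elicit adverse events, since no such purpose is stated.

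The size is unknown. The illustrative ratios run from 1.0 to about 1.8, and they are close to 1.0 (1.03 to 1.07) if the shared routes already detect 90% of events. The upper end needs weak shared detection and an effective alert. The primary analysis of pain intensity is untouched. The change is worth making before recruitment, which the article says had not begun at submission.

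**What to change.** In the adverse event monitoring section:

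1. State that the same scripted adverse-event question is asked of every participant, in both arms, at the monthly check-ins and at week 13. In the fidelity and adherence section, state outright that the check-ins cover both arms, because that sentence now sits in the paragraph on control engagement.
2. Record the detection source of each event: solicited, spontaneous or alert.
3. Use the commonly solicited events for the between-arm comparison.
4. Still report all adverse events by group, with alert-triggered events shown separately. Restricting the whole report to solicited events would drop spontaneous and alert-triggered events that the protocol undertakes to record, and could understate harm.

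The alerts stay as they are for participant protection. The cost is one extra question at contacts that already exist, one extra case report form field, and a slightly longer safety table.
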